**3.9 Data Collection**

Data are collected by the GPs in their GP practice. They are extracted on a daily basis and made available to the RCGP RSC.

RCGP RSC will make a fully anonymised data extract available to UKHSA. Each individual will be given a unique identifier that can be used to link with serology and virology data.

RCGP RSC will separately share a hashed NHS number and the unique identifier for the purposes of linking to SGSS SARS-CoV-2 positive tests, and SUS / HES hospitalisation data held by UKHSA, along with the hashing key. Once extracted, the NHS number will be deleted and data retained with the unique identifier alone to link with the anonymised GP data records.

**Table 1: Data sources for each collected variable**

| Group of Variables | Variables | Data source |
| --- | --- | --- |
| Demographic characteristics | Age on 31 August 2022 | Electronic GP record |
|  | Gender | Electronic GP record |
|  | GP practice ID | Electronic GP record |
|  | Location – NHS region | Electronic GP record |
|  | IMD quintile | Electronic GP record |
|  | Ethnicity | Electronic GP record |
| Exposure | COVID-19 vaccinations | Electronic GP record / linkage to NIMS |
|  | Dates of vaccinations | Electronic GP record / linkage to NIMS |
|  | Type of vaccine / manufacturer | Electronic GP record / linkage to NIMS |
|  | Batch numbers | Electronic GP record / linkage to NIMS |
| Outcomes TND only | Laboratory confirmed outcome | Linkage to PHE virus reference lab data |
|  | Date of swab | Linkage to PHE virus reference lab data |
|  | Date of onset | Linkage to PHE virus reference lab data |
|  | Date of receipt | Linkage to PHE virus reference lab data |
|  | Presence of fever ±10d | Electronic GP record |
|  | Presence of cough ±10d | Electronic GP record |
|  | Presence of shortness of breath ±10d | Electronic GP record |
|  | Consultation for ILI ±10d | Electronic GP record |
|  | Consultation for COVID19 ±10d | Electronic GP record |
|  | Consultation for URTI ±10d | Electronic GP record |
|  | Consultation for LRTI ±10d | Electronic GP record |
|  | Consultation for ARI ±10d | Electronic GP record |
|  | Consultation for Bronchitis ±10d | Electronic GP record |
|  | Consultation for Bronchiolitis ±10d | Electronic GP record |
|  | Consultation for asthma/COPD ±10d | Electronic GP record |
| Outcomes cohort only | Date of hospital admission | Linkage to HES / SUS data |
|  | Date of discharge | Linkage to HES / SUS data |
|  | List of ICD10 discharge codes | Linkage to HES / SUS data |
|  | Use of Oxygen | Linkage to HES / SUS data |
|  | Date of ICU admission | Linkage to HES / SUS data |
|  | Date of Death | Electronic GP record / linkage to ONS mortality data |
|  | Date of positive SARS-CoV-2 test | Linkage to SGSS / PHE virus reference lab data |
| Confounding factors | Smoking status | Electronic GP record |
|  | List of PRIMIS risk groups | Electronic GP record |
|  | Electronic Frailty Index | Electronic GP record |
|  | Indicator of living in a large residence | Electronic GP record (household key) |
|  | Cambridge Mortality Measure | Electronic GP record |
|  | Consultation count | Electronic GP record |
|  | Influenza vaccination | Electronic GP record |

The absence of any of those characteristics in the database is assumed to indicate no presence of the characteristic under study (missing values are coded absent).

Covariate values are updated on 1^st^ September of each study year on information recorded in the study database.

| Continuous update of co-variates takes place. However, some need to be defined pre-season for analysis. |
| --- |

**Procedures for database management**

| Who enters data? GPs (E), GPs and authorised practice staff (S)  Who validates data? Not validated (other than by consistency in regular analyses)  Who links database? UKHSA links to hospital (SUS/HES) and testing (SGSS) data  How are data extracted? Automated data extraction according to agreed protocol  Who centralises data? University of Oxford acts as Trusted Research Environment (TRE) for these data.  Who analyses data? UKHSA, with input from RCGP RSC  Software used? Multiple systems. The Oxford-RCGP RSC database operates in an NHS Digital – Data Security and Protection (DSP) compliant TRE. Data held in this network are stored using SQL, with extracts to fit with any required output. |
| --- |

**3.10 Sample size**

This has been assessed using the calculator below, assuming 80% power and 5% significance level.

<https://apps.p-95.com/drivesamplesize/>

**Cohort**

The plots below shows the bottom end of the 95% CI for an attack rate of 1% over the study period for sample sizes from 10,000 to 1,000,000 (note that the size of the RCGP RSC population in the smallest risk group is over 60,000). Attack rate is based on a rate of 15 cases per 10,000 population (~Nov 2020) over a 6-7 week period.

A : 60% VE

[figure not shown]

B : 90% VE

[figure not shown]

Significant VE should be detectable in subgroups with 10,000+ population (unless vaccine coverage is very low), while subgroup analyses with 100,000+ population should have reasonably high precision. The attack rate will increase over time, raising precision further.

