**1. Background**

SARS-CoV-2 vaccination was introduced in the UK on 7th December 2020. Initial clinical trial results and population studies on vaccine effectiveness (VE) showed that the vaccines were successful in preventing infection, but population studies suggest that this has lessened with antigenic change in the virus over time, though effectiveness against severe outcomes remains moderate. Continued monitoring in the wider population is important to optimize vaccination strategy to minimize the burden of disease. A large GP data source will help detect differences in VE between clinical groups.

Strong systems to evaluate the effectiveness of the COVID-19 vaccine programme will enable to:

- optimise recommendations for the use of the vaccine
- target complementary or alternative public health measures (e.g. antivirals) for population segments where vaccine is less effective.
- allow more precise estimates of the impact of current vaccination strategies on the burden of disease to support the national vaccination campaign
- evaluate COVID-19 vaccines to better understand optimal composition; use of adjuvants; need for booster doses.
- better manage and respond to reports of vaccine failures.
- counterbalance the reports of adverse events following immunisation by providing elements for an adequate risk management and cost-effectiveness analysis.

This proposal concerns the use of the established general practice database maintained by the Oxford-Royal College of General Practitioners (RCGP) Research and Surveillance Centre (RSC), one of Europe’s oldest sentinel systems.^[[1]](#footnote-1)^ The RCGP RSC has supported and collaborated with Public Health England and predecessor bodies for over 50 years and adapted significantly to meet the challenges of the pandemic.^[[2]](#footnote-2),^^[[3]](#footnote-3)^

We will use cohort and case-control methods to estimate COVID-19 VE against a range of clinical and virological endpoints, with a focus on the 2022 Autumn, 2023 Spring and 2023 Autumn booster programmes.

We propose the dataset for analysis aims to include:

1] The inclusion of results of laboratory tests via both Pillar testing and Sentinel surveillance, both historical and current.

2] Information on the type and dose of vaccine given, manufacturer and batch number.

3] Patient specific information on demographic variables, risk group status and prior influenza vaccine history.

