**3. Methods**

**3.1 Study designs**

For 2023/24 RCGP RSC and UKHSA in collaboration will use two main study designs to estimate COVID-19 vaccine effectiveness in England across all age groups, and in sub-populations for individuals registered with participating GPs in the RCGP RSC sentinel network. The primary designs to be used are as follows:

- Cohort study with primary outcomes hospitalisation and death.
- Test-negative design (TND) study on patients within the sentinel swabbing scheme.

This proposal covers both the cohort study and the TND study.

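### The cohort's 10,000+ and 100,000+ subgroup thresholds are calculated from a COVID-19 case rate, so they are unsupported for the outcomes the cohort analyses: hospitalisation and death

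*Protocol*

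**What the plan says.** Section 3.10 sets the calculation up "assuming 80% power and 5% significance level". For the cohort it plots "the bottom end of the 95% CI for an attack rate of 1% over the study period for sample sizes from 10,000 to 1,000,000", at VE of 60% and of 90%. The source of the 1% is "Attack rate is based on a rate of 15 cases per 10,000 population (~Nov 2020) over a 6-7 week period". The same section puts the smallest risk group at over 60,000 people.

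Three conclusions follow there:
- "Significant VE should be detectable in subgroups with 10,000+ population (unless vaccine coverage is very low");
- "subgroup analyses with 100,000+ population should have reasonably high precision";
- "The attack rate will increase over time, raising precision further".

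Section 3.1 describes the design as "Cohort study with primary outcomes hospitalisation and death". Section 3.6 restricts the primary hospitalisation analysis to coded COVID-19 admissions of 2 nights or longer and defines death by a COVID-19 code on the certificate. Section 3.12 plans cohort models for those two outcomes only, with people vaccinated six months or more ago as the baseline.

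**The concern.** The rate that drives the calculation belongs to a different endpoint from the one analysed. Section 3.2.1 lists outcomes and cases of COVID-19 as separate items to be identified in the records, and the only formal case definition, in Section 3.6, is a positive swab in the test-negative study. No cohort analysis of cases is planned. Hospital stays of 2 nights or more and deaths will be rarer than cases, and precision is governed by the number of events. The rate also dates from about November 2020, before vaccination began on 7 December 2020 (Section 1).

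VE by specific clinical risk group is a primary objective (Section 2.2), and the thresholds are the protocol's only guidance on which cohort subgroups can support an estimate. A reader may rely on them for strata that are too small for the outcome.

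**Working it through.** **Inputs from the protocol.** Attack rate 1%; VE 60% and 90%; N of 10,000 and 100,000; smallest risk group 60,000; 5% significance, taken as two-sided to match the 95% interval; 80% power. Follow-up is 30 weeks for Autumn 2022 (5 September 2022 to 2 April 2023) and 22 weeks for Spring 2023 (3 April to 3 September), from Section 3.4.

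**Assumptions.** Coverage c = 50%, because the plots are not available to me. Outcome risks below 1% are illustrative.

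**Step 1: the 1%.** 15/10,000 × 6 = 0.90% and 15/10,000 × 7 = 1.05%. The 1% reproduces if the rate is per week.

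**Step 2: the plan's threshold.** Let AR be the cumulative risk in the unvaccinated. Expected events are u = N(1−c)AR in the unvaccinated and v = N·c·AR(1−VE) in the vaccinated. The lower limit of VE is 1 − (1−VE)·exp(1.96·√(1/u + 1/v)).

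For N = 10,000, AR = 1% and VE = 60%: u = 50, v = 20, √(0.02 + 0.05) = 0.265, and the limit is 1 − 0.4 × 1.68 = 33%. A two-proportion calculation gives 95% power. The 10,000+ statement therefore follows from a 1% risk at this coverage. At 90% coverage the power is 69%, and the plan's caveat mentions only very low coverage.

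**Step 3: dependence on the outcome risk.** At fixed VE and coverage, the limit depends only on N × AR. Expected lower limits for VE 60%:

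| Outcome risk | N = 10,000 | N = 60,000 | N = 100,000 |
|---|---|---|---|
| 1% (the plan) | 33% | 51% | 53% |
| 0.10% (assumed) | −106% | 22% | 33% |
| 0.02% (assumed) | not calculated (2 expected events with no vaccination) | −79% | −28% |

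At 0.10%, two-proportion power is 20%, 79% and 95% for the three sizes.

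**Step 4: break-even risks.** With c = 0.5 and VE = 60%, the variance of the log rate ratio is (2/(N·AR))(1 + 1/0.4) = 7/(N·AR), and |ln 0.4| = 0.916.
- Limit at zero: 7/(N·AR) = (0.916/1.96)² = 0.2186, so N·AR = 32.
- 80% power: 7/(N·AR) = (0.916/2.80)² = 0.1071, so N·AR = 65.

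| N | Limit excludes zero | 80% power |
|---|---|---|
| 10,000 | 0.32% | 0.65% (0.61% by two proportions) |
| 60,000 | 0.053% | 0.11% (0.10% by two proportions) |

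At VE 90%, the two-proportion figure for 80% power at N = 10,000 is 0.21%. At VE 40%, an illustrative lower value, the variance is 5.33/(N·AR). The break-evens are then 0.79% and 1.6% at 10,000, and 0.13% and 0.27% at 60,000.

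**Step 5: longer follow-up.** At the plan's weekly case rate, 22 weeks gives 22 × 0.15% = 3.3% and 30 weeks gives 4.5%. To reach 0.61% at N = 10,000, the severe share of cases would have to be 0.61/3.3 = 18% or 0.61/4.5 = 13.5%. To reach 0.11% at N = 60,000, it would have to be 3.3% or 2.4%.

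**The case against.** Much of the other side's case stands. The arithmetic in Section 3.10 is internally sound. The missing time unit is clerical, because the stated 1% fixes the rate as weekly; the 0.15% that results from reading it without the unit is not what the plan means. The evaluations last 22-30 weeks rather than 6-7, and Section 3.2 restricts them to older, immunosuppressed or clinical-risk groups, whose severe-outcome risk may be well above that of the general population. No whole risk group is as small as 10,000. Section 4.3 already warns of wide intervals in some sub-analyses. The cohort takes in the whole registered population, so no recruitment target or estimate depends on this calculation, and poor precision would be visible in the reported intervals.

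These points limit the concern but do not remove it. Section 4.3 is generic and corrects neither the rate nor the thresholds. Longer follow-up helps, but the protocol never shows that the break-even risks are reached. Exposure is also to be split by vaccine type and time since dose (Section 3.5), and some risk groups may be subdivided (Section 3.7), so fewer events inform each contrast than the table assumes.

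A reader might infer that the 10,000+ claim is false for hospitalisation and death. The protocol cannot show that, because it states neither rate. A reader might also take Section 1 to contradict a planning VE of 60%. It does not: the decline described there concerns infection, and for severe disease the text reads "though effectiveness against severe outcomes remains moderate".

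**Conclusion.** The concern holds as a mismatch of endpoint. The 10,000+ and 100,000+ statements are derived from a case rate and have no stated basis for hospitalisation or death. At VE 60% and 50% coverage, the 10,000 threshold needs a cumulative outcome risk of about 0.32% for the expected interval to exclude zero and about 0.6-0.65% for 80% power. A whole risk group of 60,000 needs only about 0.05% and 0.11%. The weakness therefore falls mainly on finer strata and on death, which I assume is rarer than hospitalisation.

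The mismatch is certain from the text; its consequence in any given group is not. The break-evens rest on the assumed coverage and on a single vaccinated-versus-unvaccinated contrast, and the formulas are rough when few events are expected. The passage should be corrected, but it biases no estimate and does not threaten the validity of the analysis.

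**What to change.** Recompute the cohort plots separately for hospitalisation of 2 nights or more and for death. Use rates observed in the linked data for the eligible groups, over the planned 22-30 week periods. Keep the existing VE scenarios if wanted, but add a lower one suited to the incremental comparison with people vaccinated six months or more ago (Section 3.12). The protocol gives no value for it, so its source should be stated.

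Replace the 10,000+ and 100,000+ thresholds with the resulting minimum size for each outcome. If the 15 per 10,000 figure is kept anywhere, say that it is per week.

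The work is one rerun of the calculator and a short rewrite, with no new data collection. The price is that the stated precision becomes less favourable.

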**3.6 Outcome(s)**

**Outcomes for Cohort Studies of Severe Disease**

Linkage with ONS mortality data, Hospital Episode Statistics (HES) and/or Secondary Uses Service (SUS), should provide the following additional outcomes:

- A COVID-19 hospitalisation will be defined as hospital admission, with
  - a primary COVID-19 discharge code present. (ICD10 U07.1, U07.2, U07.4 or U07.5)
  - a primary acute respiratory code (J04, J09-J22, J80), in conjunction with BOTH a secondary COVID-19 discharge code AND a record of a positive SARS-CoV-2 test -14 to +2 days around admission (to ensure infection prior to hospitalisation)
  - consecutive admissions with the same primary code will be aggregated and the primary hospitalisations analysis will include only stays of 2 nights or longer
- Stays of any length will be evaluated in a secondary analysis
- A very severe hospitalisation definition including use of Oxygen or admission to intensive care in addition to the primary definition above will also be evaluated in a secondary analysis.
- A COVID-19 death will be defined as a death with a COVID-19 ICD10 code on the death certificate (in any position)
- A definition including additional deaths occurring within 28 days of a positive test will also be used in a secondary analysis.

Negative controls do not need to be identified.

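### The cohort precision statement rests on a COVID-19 case rate over 6-7 weeks, so its 10,000 and 100,000 subgroup thresholds are not supported for hospitalisation and death

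*Protocol*

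**What the plan says.** All references are to the COVID-19 study in the protocol. Section 3.10 states that sample size was assessed "assuming 80% power and 5% significance level". For the cohort it plots the lower end of the 95% confidence interval at VE 60% and VE 90%, for an "attack rate of 1% over the study period for sample sizes from 10,000 to 1,000,000". The source of that rate is given as "Attack rate is based on a rate of 15 cases per 10,000 population (~Nov 2020) over a 6-7 week period".

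Two conclusions follow in the same paragraph. The first is "Significant VE should be detectable in subgroups with 10,000+ population (unless vaccine coverage is very low". The second is that "subgroup analyses with 100,000+ population should have reasonably high precision". The text also notes that "the size of the RCGP RSC population in the smallest risk group is over 60,000", and that the attack rate will rise with time.

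The outcomes are set elsewhere. Section 3.1 describes a "Cohort study with primary outcomes hospitalisation and death". Section 3.6 defines both as severe-disease outcomes and says that "the primary hospitalisations analysis will include only stays of 2 nights or longer". Stays of any length, very severe admissions and deaths within 28 days of a positive test are secondary. Section 3.12 runs the cohort models for hospitalisation and death. Section 3.4 sets the Autumn 2022 window at 5 September 2022 to 2 April 2023 (30 weeks) and the Spring 2023 window at 3 April to 3 September 2023 (22 weeks).

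**The concern.** Precision of a relative risk depends on the number of events, not on the number of people. The plots take their events from a rate of cases, whereas the cohort counts only admissions and deaths. Unless every case is admitted or dies, the severe-outcome rate over the same period is lower than the case rate, and the population needed for given precision rises in inverse proportion. Section 3.10 contains no hospitalisation or death rate, so the thresholds belong to an outcome that the cohort does not analyse.

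That cases means test-positive infection is an inference, but a firm one. Section 3.6 defines a case for the test-negative study by a positive SARS-CoV-2 test, and the companion plots in 3.10 are benchmarked to swab positivity in the same month, November 2020. Read as admissions, the figure would put 1% of the registered population in hospital within 6-7 weeks, which nothing in the protocol supports.

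VE by clinical risk group is a primary objective (2.2). A reader who relies on the 10,000 figure, and sees that the smallest risk group exceeds 60,000, would expect a significant result in every group. A wide interval for admission or death could then be taken as lack of effect.

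**Working it through.** **Inputs from the protocol.** 15 cases per 10,000; 6-7 weeks; VE 60% (RR 0.40) and VE 90% (RR 0.10); 80% power; 5% significance, taken as two-sided; subgroup sizes 10,000, 60,000 and 100,000; windows of 22 and 30 weeks.

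**Assumptions.** Coverage c = 50%, because the figures are not shown. Fixed boosted and unboosted groups with the attack rate a applied to the unboosted. The severe-outcome rate is shown as a range, because the protocol gives none.

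**Step 1: the plan's own figures.** 15/10,000 × 6 = 0.90% and 15/10,000 × 7 = 1.05%, so 1% follows if the rate is weekly. Read as a cumulative total it would be 0.15%. At a = 1% and VE 60%, a two-proportion calculation needs 6,060 people in total at 50% coverage, 8,370 at 80% and 18,688 at 10%. So 10,000 is enough for cases unless coverage is very low, as the protocol says.

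**Step 2: break-even rate.** Expected events are u = n(1-c)a in the unboosted and v = n·c·a·RR in the boosted. With SE(ln RR) = √(1/u + 1/v), the requirement is

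n·a = [1/(1-c) + 1/(c·RR)] × (z/ln RR)².

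At c = 0.5 and RR = 0.40 the bracket is 2 + 5 = 7, and ln 0.40 = -0.916.

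- Lower bound above zero (z = 1.96): n·a = 32.0. At n = 10,000 this means a ≥ 0.32%. Events: 16.0 + 6.4, about 22.
- 80% power (z = 2.80): n·a = 65.4. At n = 10,000 this means a ≥ 0.65%; the two-proportion method gives 0.60%. Events: 32.7 + 13.1, about 46.
- At n = 100,000 the same requirements are 0.032% and about 0.06-0.07%.
- At 80% coverage, 80% power with n = 10,000 needs 0.83% (two-proportion method).
- At VE 90% and 50% coverage, 80% power with n = 10,000 needs about 0.21% (two-proportion) to 0.33% (log relative risk).

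**Step 3: precision over a range of rates.** Limits for VE are 1 - RR·exp(±1.96·SE), at VE 60% and 50% coverage.

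| Rate in unboosted | n = 10,000: events u + v | n = 10,000: lower bound | n = 60,000: lower bound | n = 100,000: 95% CI |
|---|---|---|---|---|
| 1% (as stated, cases) | 50 + 20 | 33% | 51% | 53 to 66% |
| 0.45% | 22.5 + 9 | 13% | 45% | 49 to 69% |
| 0.33% | 16.5 + 6.6 | 1% | 42% | 47 to 70% |
| 0.1% | 5 + 2 | -106% | 22% | 33 to 76% |
| 0.05% | 2.5 + 1 | -307% | -3% | 17 to 81% |
| 0.02% | 1 + 0.4 | not informative | below 0 | -28 to 87% |

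Example, n = 10,000 at 0.1%: SE = √(1/5 + 1/2) = 0.837; 0.40 × exp(1.96 × 0.837) = 2.06; bound = -106%.

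**Step 4: the actual windows.** The same weekly case rate gives 15/10,000 × 22 = 3.3% and × 30 = 4.5% cases. If one case in ten had the severe outcome (an assumption), a would be 0.33-0.45%, the second and third rows of the table. To reach 0.60-0.65%, between 0.60/4.5 = 13% and 0.65/3.3 = 20% of cases would have to be admitted for two nights or more, or die.

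**The case against.** The strongest reply is follow-up time. The windows last 22-30 weeks, and 3.10 itself expects the attack rate to grow. With one case in ten severe, the bound at 10,000 is +1% to +13%, and at 60,000 it is 42-45%. The target groups are also older or at higher clinical risk. This stands as a reason not to present the negative bounds in the lower rows as forecasts. It does not rescue the 10,000 threshold: power in that scenario is only 51-64%, and the protocol makes no such calculation. The exposure categories by time since dose and vaccine type (3.5, 3.12) pull the other way by dividing the boosted events further.

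Second, section 4.3 concedes that some sub-analyses may have wide intervals. That is true but generic, and it does not withdraw the two explicit thresholds.

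Third, the cohort is the whole registered population of about 18.8 million, so the calculation sets no recruitment target. This stands. What is affected is what readers are told to expect, not the design or the analysis.

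A reader might go further and infer that 100,000 is also far too small. The documents do not show this. With no severe-outcome rate given it cannot be computed, and at an assumed 0.1% the interval of 33-76% is clearly significant. A reader might also infer that the section promises high precision for every risk group. It does not: that promise is tied to 100,000 or more, and the smallest group is only said to exceed 60,000. Nor is there an arithmetic slip, since the 1% reproduces.

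**Conclusion.** The point holds as a mismatch of outcome and follow-up. The precision statement is calculated for cases over 6-7 weeks, while the cohort analyses admissions and deaths over 22-30 weeks.

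For significance at 10,000 the claim is unsupported: at VE 60% and 50% coverage it has 80% power only if the severe-outcome rate is about 0.60-0.65%, and a bound above zero needs about 0.32%. For 100,000 the conclusion depends on the rate. Significance survives at 0.1% and 0.05% but is gone by about 0.02%, and the interval widens from 53-66% at the stated 1% to 33-76% and 17-81%.

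The break-even rates rest on the assumed coverage and on fixed exposure groups. The intervals rest also on assumed severe-outcome rates. The mismatch itself needs none of these assumptions.

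**What to change.** Recalculate the cohort part of 3.10 separately for hospitalisation of two nights or more and for death, using event rates and follow-up from the completed Autumn 2022 window in the target groups. Replace the sentence with the 10,000 and 100,000 thresholds by required event counts. At VE 60% and 50% coverage these are about 22 events (16 unboosted, 6 boosted) for a lower bound above zero and about 46 (33 and 13) for 80% power, with counterparts at the coverage actually seen. State which risk groups reach these counts for each outcome, and note that splitting by time since dose and vaccine type raises the requirement.

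The cost is one recalculation and some rewording. The stated precision becomes less favourable. No more patients are needed.
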